### Sample size

Although several studies have investigated the effects of acupuncture on cancer and related symptoms, few RCTs have assessed the effects of EA on CIPN. There is no previous study on which to base the sample size calculation. Therefore, this pilot study will evaluate the efficacy and safety of EA and the feasibility of clinical trials. The findings will also provide data about the variability of the primary and secondary outcomes, thereby facilitating the performance of power calculations for full-scale RCTs. Taking into account the minimum number of subjects necessary to assess the effects of EA, we calculated a total sample size of 40 patients, 20 in each group [28,29].

### Data analysis

The clinical effects of EA on CIPN will be analyzed on an intent-to-treat (ITT) basis. Missing values will be imputed by the last observation carried forward method. The results of the ITT analysis will be compared with those of per-protocol (PP) analysis to evaluate the sensitivity.

Baseline demographic and clinical characteristics of patients will be reported as mean (standard deviation or 95% confidence intervals) or as maximum or minimum for continuous variables, and as frequencies and percentages for categorical variables. Continuous variables will be analyzed by two-sample *t*-tests or Wilcoxon rank sum tests, and categorical variables will be analyzed using the chi-squared or Fisher’s exact test, according to whether or not the data are normally distributed.

Between group differences in primary and secondary outcomes will be analyzed by analysis of covariance, with the baseline score and centers as the covariates and current use of chemotherapy or neuropathy medication as stratified variables, at the second, fourth (primary endpoint), eighth and twelfth weeks. The results for the stratified groups will be compared with the results for the whole subject pool (non-stratified) to determine whether current use of chemotherapy or neuropathy medication is a suitable stratification factor that affects the treatment outcome. Mean differences from baseline to post-treatment in each group will be assessed using paired *t*-tests or Wilcoxon signed rank tests. Repeated measures analysis of variance will be used for assessments at different time points. All statistical analyses will be performed using SAS version 9.1.3 (SAS institute Inc., Cary, NC, USA) by a statistician blinded to patient allocation, and a significance level of 0.05 will be used.

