### Randomization and allocation concealment

A total of 40 participants who meet the eligibility criteria will be randomised in a ratio of 1:1 to the EA or sham EA group. In this trial, constant exposure to neurotoxic agents and concomitant use of neuropathy medications during the study are variables that present potential confounding effects for the study results. Therefore, this randomization will be stratified according to the receipt of on-going chemotherapy during enrollment or completion of therapy and according to the use of medication for neuropathy. Patients will be randomized using a computer-generated random allocation sequence through the stratified block randomization method of SAS version 9.1.3 (SAS Institute Inc., Cary, NC, USA) by a statistician ([name]) with no clinical involvement in this trial. Sequentially numbered opaque sealed envelopes containing the randomization assignments will be delivered to the clinical trial center. Allocation concealment will not be broken until the final data analysis report is completed.

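### Last observation carried forward, the only missing-data method named, can bias the week-4 comparison in either direction, and no planned analysis tests its assumption

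*Protocol article*

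**What the plan says.** The Data analysis section sets the population first: "The clinical effects of EA on CIPN will be analyzed on an intent-to-treat (ITT) basis". It then fixes the handling of gaps: "Missing values will be imputed by the last observation carried forward method". No exception is made by outcome or visit. The only sensitivity check follows: "The results of the ITT analysis will be compared with those of per-protocol (PP) analysis to evaluate the sensitivity".

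The main model is: "Between group differences in primary and secondary outcomes will be analyzed by analysis of covariance, with the baseline score and centers as the covariates". It is applied "at the second, fourth (primary endpoint), eighth and twelfth weeks". The section adds: "Repeated measures analysis of variance will be used for assessments at different time points".

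Four other places bear on this:

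- **Participants, Inclusion criteria:** patients still receiving neurotoxic chemotherapy may enter, and a patient who needs a different type or dose of neuropathy medication is withdrawn.
- **Randomization and allocation concealment:** "constant exposure to neurotoxic agents and concomitant use of neuropathy medications during the study are variables that present potential confounding effects". Both factors are used as strata.
- **Table 1:** QLQ-CIPN20 is recorded at baseline and weeks 2, 4, 8 and 12. Nerve conduction (NCS) is recorded at baseline and week 12 only.
- **Sample size:** "The findings will also provide data about the variability of the primary and secondary outcomes". These data are to feed the power calculations of full-scale trials.

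**The concern.** Last observation carried forward (LOCF) treats a patient's score as unchanged from the last visit attended. Three features of the protocol make that hard to accept.

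- Patients under continuing neurotoxic exposure may still be getting worse.
- The withdrawal rule links leaving the study to a changed need for neuropathy medication, so dropout may depend on the outcome and may differ by arm.
- The value carried into week 4 comes from mid-treatment or from before treatment.

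For NCS the rule is baseline carried forward, so every patient with a missing week-12 study is given a change of exactly zero.

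At stake is the week-4 contrast, which is the primary estimate. The effect estimate passed on to a larger trial would be affected too. The per-protocol comparison removes patients; it does not replace the constant-score assumption with another one.

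**Working it through.** **Inputs.** From the article: 20 patients per arm, QLQ-CIPN20 at baseline, week 2 and week 4, ANCOVA on baseline, significance level 0.05 (taken as two-sided). The article gives no dropout rate, SD, correlation or expected course, so there is no figure of its own to reproduce. Everything else below is assumed. Higher scores are worse, so a negative EA − sham difference favours EA.

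- *Set A:* 0–100 score, SD 20, correlation 0.89 over 2 weeks and 0.80 over 4 weeks, dropout after week 2.
- *Set B:* 0–100 score, SD 15, correlation 0.7 between successive visits, half the dropouts leaving with baseline only and half after week 2, effect half reached at week 2.
- Each scenario was simulated 6,000 times.

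**Formula.** Let p be the dropout proportion in an arm and m the mean change that dropouts miss between their last score and week 4. If dropout is random within arm:

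expected LOCF difference = true difference − (p_EA × m_EA − p_sham × m_sham)

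**Set A, no true effect**

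| Common drift, weeks 2–4 | Dropout EA / sham | Formula | Simulated |
|---|---|---|---|
| +7 | 25% / 5% | −(0.25×7 − 0.05×7) = −1.4 | −1.4 |
| −9 | 25% / 5% | −(0.25×(−9) − 0.05×(−9)) = +1.8 | +1.7 to +1.8 |
| +7 | 15% / 5% | −(0.15×7 − 0.05×7) = −0.7 | −0.6 |
| +7 | 10% / 10% | 0 | 0.0 |

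The first row is a false benefit of EA and the second a false harm. Rejection rates in the four rows were 6.5%, 7.9%, 5.2% and 5.1%.

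**Set A, true effect −10, 20% dropout in both arms.** If half the effect is present at week 2, dropouts miss −5: −10 − 0.20×(−5) = −9.0, a 10% loss. The simulated value was also −9.0. Runs with a later onset gave −8.4 to −8.5, a 15–16% loss. That corresponds to −7.5 to −8 still to come after week 2 (1.5/0.20 = 7.5; 1.6/0.20 = 8).

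An estimator that assumes missing at random and uses the baseline and week-2 scores gave about 0, 0 and −10 in the +7, −9 and true-effect scenarios.

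**Set B, true effect −10, equal dropout.** The mean missed difference is 0.5×(−10) + 0.5×(−5) = −7.5.

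| Dropout | Formula | Simulated | Power (complete data 64–65%) |
|---|---|---|---|
| 10% | −10 + 0.75 = −9.25 | −9.3 | 59% |
| 20% | −10 + 1.50 = −8.50 | −8.5 | 53% |
| 30% | −10 + 2.25 = −7.75 | −7.7 | 47% |

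**Standard errors and SD.** In Set A the complete-data standard error is 20×√(1−0.80²)×√(2/20) = 12×0.316 = 3.79. In the two null scenarios with 25% v 5% dropout, the LOCF model standard error was 3.78 and 3.81, against an empirical 3.78 and 3.84, so it was not understated. A gap appears when dropout is made more likely in worsening patients. In Set B with no effect, both arms worsening by 5 and 10% v 30% dropout, the model standard error was 3.78 against 4.15 (3.78/4.15 = 0.91). The spurious difference was 2.0 points and the type I error 10.3%. Residual SD was 1–5% low under random dropout and 6–9% low under outcome-related dropout.

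**NCS.** Every filled week-12 value has zero change. With random dropout p, an arm's mean change is multiplied by (1 − p); at 20% dropout it loses 20%.

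**The case against.** The strongest reply is that this is a feasibility pilot and that nobody knows the dropout. The null-scenario biases in Set A need a fivefold imbalance in dropout plus a 7–9 point shift within two weeks. Even then they are below half a standard error (1.8/3.8 = 0.47). Stratifying on ongoing chemotherapy tends to balance the course of scores between arms. LOCF does not always cost power either: in the −9.0 scenario it had 66%, against 60% for completers only. All of this stands, and it limits how serious the point is. It does not supply a reason for assuming constant scores.

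A second reply also stands. A mixed model assumes missing at random, and the withdrawal rule may break that assumption. In a run where dropout depended on unobserved worsening, the missing-at-random estimator was biased too (−1.9, against −2.3 for LOCF). The full mixed model proposed below was not itself simulated.

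A reader might infer more than the article supports:

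- *That standard errors and SD are generally too small.* The checks show this mainly under outcome-related dropout. Even the 6–9% loss in residual SD is below the sampling error of an SD from 40 patients (about 1/√(2×38) = 11%). The article also does not say that the variability estimate will come from filled data.
- *That the protocol itself describes recovering patients or a progressive action of EA.* It says neither; the Background calls the neuropathy only partly reversible and often persistent. Only the continuing exposure and the withdrawal rule carry the argument.
- *That the repeated measures ANOVA is run on filled data.* This is the natural reading, but it is not stated.
- *That the PGIC rule is wrong because its first rating is at week 4.* An early dropout has nothing to carry, but this is a detail that an article may leave to the full plan.

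**Conclusion.** The point holds as a badly fixed method, not as an omission: the article names LOCF outright for the analysis that contains the primary contrast. LOCF can bias the week-4 difference in either direction, so it cannot be defended as conservative. Under Set A the size is a 10–16% shrinkage of a true −10 effect at 20% dropout, or a spurious 1.4–1.8 points with no effect, 25% v 5% dropout and a 7–9 point drift. These sizes depend wholly on assumed dropout, SD and course. The bias is zero when there is no effect and both arms share the same dropout and course. Understated standard errors and SD are a possible and modest further effect, mainly when dropout is related to outcome. In a pilot of this size the point should be fixed before unblinding, but it does not put the trial in question.

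**What to change.** Replace LOCF and the repeated measures ANOVA with one likelihood-based mixed model for repeated measures, fitted to the observed scores at weeks 2, 4, 8 and 12. Include arm, visit, arm-by-visit, baseline score, centre and both randomisation strata, with Kenward-Roger degrees of freedom. Because there are only 40 patients, name in advance a simpler covariance structure to use if the unstructured one fails to converge. State the week-4 arm contrast as the primary estimate.

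Add a delta-shift or reference-based imputation analysis, because the withdrawal rule may make dropout depend on worsening that is never recorded. Keep the per-protocol analysis as supplementary, and LOCF too if it is wanted for comparison. For NCS, which has one post-baseline visit, drop baseline carried forward and analyse the observed week-12 values.

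The cost is analysis wording. No visits or patients are added, and the article reports that recruitment was still under way. The standard error of the week-4 contrast rises slightly: in Set A it was about 4.1 points for the missing-at-random estimator, against 3.7–3.8 for LOCF.

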## Methods/design

### Study design and ethics

This is a patient-assessor-blinded, randomized, sham-controlled clinical trial with two parallel arms. The trial will be conducted at two clinical research centers in Korea; Kyung Hee University Hospital at Gangdong and Dongguk University Ilsan Oriental Hospital, in accordance with the Declaration of Helsinki and the Guidelines for Good Clinical Practice. This research protocol has been reviewed and approved by the institutional review boards (IRB) of each trial center (KHNMC-OH-IRB 2012-007 and 2012-01). Written informed consent will be obtained from all study participants prior to enrollment. Eligible participants will be randomized in a ratio of 1:1 to the EA or sham EA arm and receive treatment for four weeks. Patients will be followed-up for two months thereafter (Figure 1). Participants will be evaluated and results will be analyzed by professionals blinded to group allocation. This protocol has been registered with the ‘Clinical Research Information Service’ of the Republic of Korea, a registry in the WHO Registry Network.

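### The only method named for all visits together is a repeated measures ANOVA with no covariates stated; if fitted unadjusted, this supporting analysis can lose substantial power that baseline adjustment would recover

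*Protocol article*

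**What the plan says.** In the protocol article, Data analysis, between-arm differences in the primary and secondary outcomes are tested by analysis of covariance, "with the baseline score and centers as the covariates and current use of chemotherapy or neuropathy medication as stratified variables". This is done separately at weeks 2, 4, 8 and 12, and week 4 is marked as the primary endpoint. Within-arm changes from baseline get paired tests. Then comes one sentence on the visits taken together: "Repeated measures analysis of variance will be used for assessments at different time points". It does not name covariates, say which effect is tested, or say whether baseline counts as a time level.

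Under Randomization and allocation concealment, ongoing chemotherapy and neuropathy medication are described as potential confounders, and "this randomization will be stratified according to the receipt of on-going chemotherapy during enrollment or completion of therapy", with neuropathy medication as the second factor.

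Table 1 places QLQ-CIPN20, SWM and QLQ-C30 at baseline and weeks 2, 4, 8 and 12. NRS is recorded 11 times, 10 of them after baseline.

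**The concern.** The same paragraph uses analysis of covariance where it wants adjustment and analysis of variance for the all-visit method. The natural reading is that the second model has neither baseline nor the design factors. It could then be fitted in two ways:

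- With baseline as one of the time levels, the arm effect is averaged with a visit at which the arms differ only by chance, and the treatment signal moves into an arm-by-time test on 4 degrees of freedom.
- With baseline left out, what it tells us about later scores is lost.

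Neither problem needs missing data to arise. At stake is a time-course result that looks weaker than the adjusted week-4 result only because a weaker model was used, in a trial of 40 patients that already records every variable needed to avoid this.

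**Working it through.** **Inputs from the article.** Size: "we calculated a total sample size of 40 patients, 20 in each group"; "Eligible participants will be randomized in a ratio of 1:1 to the EA or sham EA arm"; "a significance level of 0.05 will be used" (two-sided assumed). Visits at weeks 0, 2, 4, 8 and 12 come from Table 1.

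**Inputs that must be assumed.** The article gives no effect size, SD, power or correlation: "There is no previous study on which to base the sample size calculation", and on variability, "The findings will also provide data about the variability of the primary and secondary outcomes". I set SD = 1, complete data, difference d and between-visit correlation ρ. The main case is d = 0.7 at every post-baseline visit and ρ = 0.6 between every pair of visits (compound symmetry).

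**The plan's own figure.** No power calculation lies behind the 40 patients, so there is none to reproduce. For scale, by the normal approximation 20 per arm gives 80% power in a simple two-group comparison at (1.960 + 0.842) × √(2/20) = 0.89 SD.

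**Main case.**

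1. *Arm effect, post-baseline visits, unadjusted.* Variance of a patient's four-visit mean = (1 + 3ρ)/4 = 0.70. SE of the difference = √(2 × 0.70/20) = 0.265. Noncentrality = 0.7/0.265 = 2.65 on 38 df. Power about 73%.
2. *Arm effect, baseline as a level.* Difference = 0.7 × 4/5 = 0.56. Variance = (1 + 4ρ)/5 = 0.68. SE = √(2 × 0.68/20) = 0.261. Noncentrality = 2.15. Power about 55%.
3. *Arm-by-time, baseline as a level.* λ = (n/2) × Σ(d_j − mean d)²/(1 − ρ) = 10 × (0.56² + 4 × 0.14²)/0.4 = 10 × 0.392/0.4 = 9.8 on 4 and 152 df. Power about 69%; 67% in the ruling simulation.
4. *Arm effect, baseline as covariate.* Variance = 0.70 − ρ² = 0.70 − 0.36 = 0.34. SE = √(2 × 0.34/20) = 0.184. Noncentrality = 3.80 on 37 df. Power about 96%; 95% in simulation, which also carries the cost of chance baseline imbalance.

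The variance ratio is 0.70/0.34 = 2.06, so the unadjusted post-baseline test needs about twice the patients for the same precision.

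**How far the answer moves.** Power at d = 0.5, compound symmetry:

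| ρ | Post-baseline, unadjusted | Baseline as a level | Arm-by-time | Baseline as covariate |
|---|---|---|---|---|
| 0.3 | 0.61 | 0.46 | 0.23 | 0.70 |
| 0.5 | 0.50 | 0.36 | 0.31 | 0.71 |
| 0.6 | 0.45 | 0.32 | 0.38 | 0.75 |
| 0.7 | 0.42 | 0.29 | 0.50 | 0.82 |
| 0.8 | 0.39 | 0.27 | 0.70 | 0.92 |

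In simulation at ρ = 0.6 and d = 0.5, the unadjusted four-visit arm effect (0.455) has slightly less power than the single-visit week-4 ANCOVA (0.477): the three further visits gain nothing until baseline enters.

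With first-order autoregressive correlation of 0.3 between adjacent visits, the post-baseline loss almost vanishes: 0.70 against 0.71 at d = 0.5, and 0.98 against 0.98 at d = 0.8. At d = 0.8 and compound symmetry 0.8, arm-by-time loses only about 1 point. Across the cases examined the loss runs from about 0 to 65 points.

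**Centre and strata.** Three further df change power by less than 1 point if these terms explain no residual variance. If they explain 5 to 30% of it, power goes from 0.988 to between 0.991 and 0.999 at d = 0.8, ρ = 0.6, a case already near its ceiling.

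**The case against.** **The defect is inferred.** A reader might conclude that the plan excludes the covariates. It does not say so; it is silent, and a full protocol or analysis plan that is not shown may supply the terms. That stands as a limit on the wording. But the article lists the terms for one analysis and names a different method for the other, so this is a named method with a better alternative, not only a missing detail.

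**It may not compare arms.** The sentence follows the within-arm paired tests and could describe change over time. If so, the power figures do not apply, and the article names no between-arm analysis that uses all visits together.

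**The effect may fade after treatment ends at week 4.** With differences of 0.7, 0.7, 0.35 and 0 SD at weeks 2, 4, 8 and 12 (correlation 0.6), arm-by-time has 79% power and the adjusted mean 63%. These test different hypotheses. Like for like, the adjusted mean beats the unadjusted mean (63% against 37%), and an adjusted joint test of the arms across visits is about level with arm-by-time (81% against 79%; with 0.7, 0.7, 0 and 0 SD, 85% against 86%). What stands is that the average alone is not enough to report.

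**Type I error.** A reader might infer that the arm-by-time test is anti-conservative. Left uncorrected, with correlation that decays over time, its error was about 5.5 to 8.6% on five visits and 7 to 13% on the 11 NRS readings. The article does not say that the F test would go uncorrected, so this is no finding against it.

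**It is a supporting analysis in a pilot with no power target.** This is correct and limits the weight of the point.

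**Conclusion.** The point holds as a worthwhile improvement to a supporting analysis. If the all-visit analysis compares the arms and is fitted without covariates, power at 0.7 SD sustained over weeks 2 to 12 and correlation 0.6 is about 55%, 67% or 73%, depending on the effect tested, against about 95% with baseline as covariate.

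Effect size and correlation are assumptions, because the article gives neither. It would be too strong to say that the analysis loses much of its power as a general fact. Among the terms not named, nearly all the gain comes from baseline; the case for centre and the two strata is consistency with the design, not power.

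Nor does the point put the primary result in doubt: the week-4 comparison is already adjusted and does not depend on this sentence.

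**What to change.** Replace the repeated measures sentence with a repeated-measures analysis of covariance for QLQ-CIPN20, NRS, SWM and QLQ-C30:

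- **Data:** post-baseline visits only, four for QLQ-CIPN20, SWM and QLQ-C30 and ten readings for NRS.
- **Terms:** arm, visit, arm-by-visit, baseline score as a covariate and not as a time level, centre, and the two randomisation factors.
- **Covariance:** unstructured for the four-visit outcomes; a time-decay structure for the NRS series.
- **Reported as supporting:** the average arm difference over weeks 2 to 12, and the joint test of arm across visits, which keeps power if the effect fades.
- **Status:** state that the existing week-4 ANCOVA remains the primary analysis, so that two week-4 estimates do not compete.

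NCS (one post-baseline measurement) and PGIC (no baseline) stay outside this model. The cost is a sentence or two in the analysis section. All variables are already collected, and the planned SAS software can fit the model.

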### Safety and monitoring

All adverse events will be observed and reported by patients and researchers during each patient visit. Any expected or unexpected adverse events related to this study will be recorded and monitored until its resolution. Safety will also be assessed by performing blood tests, including complete blood count, differential count, and renal and liver function tests, at the screening visit and after the end of treatment. In addition, at each visit, vital signs will be measured, and adverse events will be recorded.

Data and safety monitoring will be conducted at periodic intervals during the study. The monitors will check study protocol compliance and informed consent documents and evaluate the progress of the trial, including participant recruitment, data quality and timeliness, and performance of the intervention at each trial site.

